These variables align well with the proposed global surgery framework to improve national surgical, obstetric, and anesthesia care provider plans [34]. In addition, the variables expand on outcomes for trauma-informed interventions [35]. All outcomes will be measured as final values but will be discussed in relation to the baseline established in our prior feasibility studies [7,30]. The comparisons of outcomes will be made at both individual and cluster levels, using mixed effects regression models.

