### Sample Size

To estimate the sample size, we used the open-source R Shiny application for cluster randomized controlled trials with a parallel design and discrete time decay correlation structures for multiple periods [36] available at [37]. Further, we assumed *t*-distribution due to plans for small sample corrections at the analysis stage in accordance with the report by Rutterford et al [38]. The study was approved for 4 years, but the core research team foresaw it feasible to actively collect data for a period of 3 years considering university semester breaks, public holidays, and unexpected events, such as COVID-19–related interruptions, which led to suspension of the trial for 12 months from March 2020 to March 2021. The 3 years (36 months) would yield 12 study periods given the planned training of cohorts of medical students on a 3-monthly basis in accordance with the average duration of internship deployment by the Ugandan Ministry of Health (1-5 months) and the average duration of surgery clinical rotation for university medical students (2 months).

Fixing the study power at 80% for a parallel cluster randomized trial with different cross-sections, considering a discrete time decay period of every 3 months for a total of 12 periods, and assuming correlations to decay with each period, we explored the minimum number of patient participants (cluster size) required per period using the R Shiny application [36]. Assuming a significance level of .05, a within-period intraclass correlation coefficient (ICC) of 0.02 (lower extreme: 0.01, upper extreme: 0.05), and a cluster autocorrelation coefficient (CAC) (ratio of between-period ICC to within-period ICC) of 0.8; allowing for varying cluster sizes with a coefficient of variation of 0.5; and considering a mean difference of 1.02 hours in prehospital transfer time and a pooled standard deviation of 1.64 hours as continuous outcomes reported in a previous observational study from the United States [39], the upper ICC and base CAC plateaued between 5 and 10 participants (Figure 2).

Considering a maximum of 10 participants per cluster period, an 80% power could be attained (Figure 3) and could be met with a total of 3 clusters per arm (Figure 4). This indicates a total of 6 study centers (clusters) drawn from a pool of 17, which reasonably represents 35.3% of Uganda’s regional referral hospitals.

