### Statistical Methods

#### Statistical Methods for Primary and Secondary Outcomes

##### Primary (Process) Outcomes

The primary (process) outcomes of (1) the time interval from the accident to hospital admission and (2) the time interval from the referral decision to hospital discharge will be compared between the intervention and control groups using a 2-sample *t* test if the data are normally distributed or a 2-sample Wilcoxon rank sum test if the data are not normally distributed. The normality of distribution will be assessed using the Shapiro-Wilks test, whereas the equality of variance will be determined using the Levene test. A difference in means of 60 minutes (1 hour) will be considered clinically meaningful in accordance with the golden hour principle [33].

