For all-cause mortality, the difference in proportions of all deaths at 90 days after injury will be compared between the intervention and control groups using the chi-square test if the expected count is >5 or the Fisher exact test at 95% CI otherwise. Lastly, we will conduct subgroup analyses to determine and control for factors associated with all-cause mortality using individual- and cluster-level between-within mixed effects regression models. The covariates will include age, sex, injury mechanism (including helmet use), mode of arrival, prehospital interval, referral decision to hospital discharge interval (dichotomized as ≤1 hour or >1 hour), prehospital first aid status, comorbidities, injury severity score based on the GCS at baseline, multiplicity of injuries, head and brain CT-based diagnosis, and neurosurgical intervention.

These variables have been found to influence outcomes following neurological trauma in previous studies [7]. All variables will be analyzed for confounding and effect modification using Mantel-Haenszel statistics to probe necessary interaction terms. Variables with *P* values of ≤0.2 in the bivariate analysis will be included in the multivariate analysis. The median (IQR) of the time to the event, that is, from the accident to death (in days), will be stratified by treatment arm, and the difference will be compared using the Wilcoxon 2-sample test. All analyses will be performed using Stata 15.0, and where appropriate, graphics, such as box plots, will be used to visualize the data.

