### Study Limitations

Despite the strengths of this trial, we anticipate some limitations. First, while the authors are ambitious to assume that the study centers are homogeneous, the heterogeneity among the 6 participating regional referral hospitals could cause bias and affect study estimates. Further, the relatively smaller number of clusters could affect the power of the study. However, randomization of 6 out of the 17 trauma centers is within the ethical constraints as this sample already represents 35.3% of Uganda’s regional referral hospitals. To overcome the statistical power bias limitation, the sample size is inflated for individual randomization to cater to the design effects in accordance with the report by Hooper et al [45]. Moreover, we plan to use mixed effects regression models, which permit adjustments for covariates at both the cluster and individual levels in a single-stage approach, and plan to use the *t* test, which is robust in terms of normality deviations. According to Borhan et al [52], mixed effects models are deemed suitable for smaller clusters in situations where the primary outcomes are continuous, which is the case in this trial. Further, we hope that the ancillary studies with mixed methods will add value to the overall interpretation of the trial results by providing data from individuals outside the health sector, such as traffic law enforcement professionals.

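### The only section that assigns a test to the two primary outcomes names t or Wilcoxon tests with no hospital adjustment, contradicting the mixed models promised elsewhere; if it governs, type I error for accident-to-admission time is about 15-40%

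*Protocol article*

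**What the plan says.** All references are to the protocol article.

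- **Primary (Process) Outcomes** is the only place that assigns a test to the two primary intervals. They are compared by a 2-sample t "test if the data are normally distributed or a 2-sample Wilcoxon rank sum test if the data are not normally distributed", with the choice made by a Shapiro-Wilk test and variances checked by a Levene test. It mentions no hospital effect, mixed model or small-sample correction. It takes a 60-minute difference in means as clinically meaningful.
- **Outcomes** says: "The comparisons of outcomes will be made at both individual and cluster levels, using mixed effects regression models". The Abstract likewise says that differences and 95% CIs will come from mixed effects models.
- **Sample Size** assumed a t-distribution "due to plans for small sample corrections at the analysis stage".
- **Study Limitations** calls mixed models suitable for few clusters when the primary outcomes are continuous, as here. In the same paragraph it plans the t test, "which is robust in terms of normality deviations".
- **Secondary (Patient) Outcomes** uses t tests for the TEFS/TOMS and GOS means, and compares mortality "using the chi-square test if the expected count is >5 or the Fisher exact test at 95% CI otherwise". For dichotomised TOMS and GOS it names an adjusted chi-square test without saying what is adjusted for. It adds mixed models for unfavorable TOMS, with treatment arm as a fixed effect and odds ratios as effect estimates, and for mortality.

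**The concern.** Patients in one hospital share staff, roads, police and referral routes, so their times are correlated. A test that treats about 500 patients per arm as independent understates the standard error of the difference between arms. Ordinary differences between hospitals can then pass for an effect of the training.

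Study Limitations defends the t test on normality, but the assumption that fails here is independence. The Wilcoxon branch assumes independence too.

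The normality switch adds a second difficulty. Time intervals are usually skewed, so with hundreds of patients the rank-sum branch is the likely one. That test does not estimate the difference in means on which the 60-minute threshold is defined.

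At stake are the P values and confidence intervals for both primary outcomes, and with them the trial's main conclusion.

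**Working it through.** **Inputs (Sample Size section).** "Assuming a significance level of .05, a within-period intraclass correlation coefficient (ICC) of 0.02 (lower extreme: 0.01, upper extreme: 0.05"); "a cluster autocorrelation coefficient (CAC) (ratio of between-period ICC to within-period ICC) of 0.8", with decay over 12 three-month periods; "allowing for varying cluster sizes with a coefficient of variation of 0.5"; three hospitals per arm; 10 patients per hospital-period. Sidedness is not stated; I assume two-sided.

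**The plan's own figure.** 3 × 12 × 10 = 360 per arm, 720 in all. 720 × (1 + 9 × 0.02) = 849.6, i.e. 850. 850 × 1.18 = 1003, or 502 per arm and about 168 per hospital (14 per period). These reproduce.

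**Step 1: average correlation between periods.** The mean of 0.8^|i−j| over 12 × 12 period pairs is 70.75/144 = 0.491.

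**Step 2: design effect of an arm mean.** DE = 1 + (N × 0.491 × (1 + CV²) − 1) × ICC, where N is patients per hospital. For N = 168, ICC 0.02, CV 0: 1 + (82.5 − 1) × 0.02 = 2.63.

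**Step 3: true type I error of the unadjusted test.** 2 × (1 − Φ(1.96/√DE)). For DE = 2.63 this is 22.7%.

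| Patients per hospital | ICC | DE, CV 0 to 0.5 | Type I error |
|---|---|---|---|
| 168 | 0.01 | 1.82 to 2.02 | 15-17% |
| 168 | 0.02 | 2.63 to 3.04 | 23-26% |
| 168 | 0.05 | 5.08 to 6.11 | 38-43% |
| 120 | 0.01 | 1.58 to 1.73 | 12-14% |
| 120 | 0.02 | 2.16 to 2.45 | 18-21% |
| 120 | 0.05 | 3.90 to 4.63 | 32-36% |

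**Simulation check (3000 trials per cell, 168 per hospital).** At ICC 0.01, 0.02 and 0.05 the t test rejected in 15%, 22-25% and 38-41% of null trials, and the Wilcoxon test in 14-15%, 21-24% and 37-40%. A t test on the six hospital means rejected in 4.6-5.7% across all simulated cells.

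**Second primary outcome.** It starts at a referral decision, and the number referred is not given. Assuming 3 per hospital-period (N = 36) and the same ICCs:

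- ICC 0.01: DE 1.17 to 1.21, type I error 7.0-7.5%
- ICC 0.02: DE 1.33 to 1.42, type I error 9-10%
- ICC 0.05: DE 1.83 to 2.06, type I error 15-17%

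**Can the section be read as a test on hospital summaries?** Not for its Wilcoxon option. With 3 versus 3 values the smallest exact two-sided P is 2/20 = 0.10, so it could never reach .05.

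**Power of a valid analysis.** For 1.02 h, SD 1.64, 360 per arm and CV 0.5, SE = 1.64 × √(2 × DE/360), referred to a noncentral t on 4 df.

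- ICC 0.02: SE 0.191, noncentrality 5.33, power 97%
- ICC 0.05: SE 0.263, noncentrality 3.88, power 82%

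The second figure agrees with the stated minimum of 80%. The allowance for unequal cluster sizes is approximate.

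**Width of the interval.** A valid 95% CI at ICC 0.02 (CV 0) is √2.63 × 2.776/1.96 = 2.3 times as wide as the unadjusted one.

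**The case against.** The strongest reply is that the protocol already commits to mixed models in three places, and that an analyst would follow those. This stands in part: the inflation is conditional. A reader might infer that the trial will certainly run at a type I error of 20-40%. The document does not support that. It contradicts itself, and the error follows only if the section naming the test governs. The range would also leave out the protocol's lower ICC, which gives 15-17%, and it cannot be carried over to referral-to-discharge time if only referred patients contribute.

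A reader might also infer that mixed models serve only to search for prognostic factors. That is not so for unfavorable TOMS, where the model estimates the effect of arm. But neither primary outcome is assigned such a model in the section that fixes its test.

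The section does not say that its tests are applied to patients, and methods of aggregation are referred to an appendix not shown here. A t test on hospital summaries would be valid, but the Wilcoxon option rules out a consistent reading of that kind.

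Finally, Study Limitations points to the inflated sample size. That serves power and does not protect an unadjusted test. Going from 120 to 168 per hospital raises its error at ICC 0.02 from 18-21% to 23-26%.

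**Conclusion.** The point holds as a contradiction with serious consequences. The protocol fixes, for both primary outcomes, a comparison that ignores the unit of randomisation, and elsewhere promises one that respects it.

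If the fixed test governs, type I error for accident-to-admission time is about 15-40% across the protocol's ICC range (43% by formula at ICC 0.05 and CV 0.5). This rests on a two-sided .05 level, the protocol's decay structure and 168 patients per hospital. For referral-to-discharge time the size is not determined by the document; 7-17% is illustrative and assumes 3 patients per hospital-period. No ICC in the stated range brings either figure back to 5%.

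The unadjusted t tests for the TOMS and GOS means and the chi-square or Fisher test for mortality share the fault, although mixed models follow for unfavorable TOMS and mortality. The rank-sum branch also fails to estimate the difference in means that the plan wants to interpret.

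**What to change.** In Primary (Process) Outcomes, name one primary analysis on a scale fixed in advance that yields the difference in mean hours: a linear mixed model with fixed effects for arm and three-month period, random effects for hospital and hospital-period, REML estimation and Kenward-Roger degrees of freedom. Give a t test on the six hospital means (4 df) as a check.

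Drop the Shapiro-Wilk and Levene switch. Keep the unadjusted t, Wilcoxon, chi-square and Fisher comparisons as descriptive only.

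Analyse TOMS, GOS and mortality by hospital-level summaries (4 df), or by mixed models with a small-sample method suited to the outcome type; Kenward-Roger is meant for linear models and should not be carried over to the binary outcomes. State what the adjusted chi-square adjusts for, or remove it. Bring the Abstract, Outcomes and Study Limitations into line.

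Date the change and record that it precedes the final analysis. This matters because follow-up ended in August 2023, an interim analysis took place in August 2022, and the allocation codes were to be opened to the biostatistician at that point.

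The cost is an amendment to the text and wider confidence intervals, about 2.3 times at ICC 0.02. No further patients are needed under the protocol's own assumptions.

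### A normality pre-test chooses between a t test and a Wilcoxon test for the primary intervals, although the trial is sized on and judged by a difference in means

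*Protocol article*

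**What the plan says.** Under Statistical Methods, Primary (Process) Outcomes, both intervals (accident to admission, referral decision to discharge) get a two-sample t test if normal and a "2-sample Wilcoxon rank sum test if the data are not normally distributed". The choice depends on the data: "The normality of distribution will be assessed using the Shapiro-Wilks test". A Levene test is added for equality of variance, without saying what follows from it.

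The same section then states the yardstick: "A difference in means of 60 minutes (1 hour) will be considered clinically meaningful". The Sample Size section uses the same kind of quantity, "considering a mean difference of 1.02 hours in prehospital transfer time and a pooled standard deviation of 1.64 hours".

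Other parts of the article point to other analyses:
- The abstract promises mixed effects models that report absolute or relative differences with 95% CIs.
- The Outcomes section says that outcome comparisons at individual and cluster level use mixed effects models.
- Study Limitations relies on mixed models and on the t test, "which is robust in terms of normality deviations".

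None of these is ranked against the pre-tested rule, and none withdraws it.

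**The concern.** The trial is planned and judged on one quantity, but the data decide whether that quantity is tested. The Wilcoxon test's null is that the two distributions are equal, and it responds to whether a patient in one arm tends to be quicker than a patient in the other. That coincides with a mean difference under a pure shift, which the protocol does not assume.

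On the Wilcoxon branch, the p-value and the 60-minute reading answer different questions. A significant result could appear when mean times are equal, and the article attaches no clinical threshold to a rank result. If the two intervals fell on different branches, the two primary results would also not be comparable in kind.

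**Working it through.** **1. The plan's own figures.** 10 patients x 12 periods x 3 clusters x 2 arms = 720. 720 x (1 + 9 x 0.02) = 849.6, or 850. 850 x 1.18 = 1003. Both stated totals reproduce. Power for a cluster-level contrast of means (1.02 h, SD 1.64 h, cluster autocorrelation 0.8, cluster-size CV 0.5, t with 4 df, two-sided 0.05) is 0.98 at ICC 0.02 and 0.87 at ICC 0.05. The stated 80% is met for a mean difference.

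**2. How often the pre-test rejects.** Inputs: SD 1.64 h (Sample Size), n = 425 (850/2). Assumed: Shapiro-Wilk at 0.05 and a mean of 2-6 h, since the protocol gives neither.

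| Shape of times | Rejection at n = 425 |
|---|---|
| Lognormal, mean 2-6 h | 100% |
| Gamma, mean 2-6 h | 98-100% |
| Normal cut at zero, recorded exactly, mean 2 / 3 h | 100% / 96% |
| Same, mean 4 / 6 h | 14-18% / about 5% |
| Same, mean 4 or 6 h, rounded to the half hour | 100% |

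The pre-test often passes only for near-normal, finely recorded times with a mean of about 4 h or more. With the SD still 1.64 h and means of 10-16 h, rejection falls to 63-95% (lognormal) and 33-71% (gamma). At n = 100 and mean 2-6 h it is 80-100% (lognormal) and 45-100% (gamma). That smaller size matters for the referral interval, whose number of patients is not given.

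**3. Does the Wilcoxon test track the mean?** Two lognormal arms, equal means of 4 h, 425 per arm, independent patients:
- With pooled SD held at 1.64 h and unequal spread, Wilcoxon rejects about 66% against 4% for Welch t.
- The rate depends on how unequal the spreads are. A check with SDs of 1.2 and 1.985 h (pooled √[(1.44 + 3.94)/2] = 1.64) gave 71% v 5%. SDs of 1.3 and 1.92 h gave 46% v 5%.
- With one SD kept at 1.64 h, an SD of 2.0 h in the other arm gives 19% v 4%, and 2.5 h gives 71% v 5%.

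**4. Is power lost if training removes long delays?** Let a fraction p of control patients be delayed by D hours, with p x D = 1.02 h. The delays add p(1 − p)D²/2 to the pooled variance, which equals 0.5202(1 − p)/p. Keeping the pooled variance at or below 1.64² = 2.6896 requires p ≥ 0.5202/(2.6896 + 0.5202) = 16.2%. For p = 17%, 18%, 20%, 25% and 30% with pooled SD 1.64 h, Wilcoxon power is 98.5-100% and t power 100%.

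Power falls only when the SD exceeds the planned one (base mean 2 h, base SD 1.64 h):

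| Control-arm delay pattern | Pooled SD | t test | Wilcoxon |
|---|---|---|---|
| 12% by 8.5 h | √(2.69 + 3.81) = 2.55 h | 100% | about 85% |
| 10% by 10.2 h | √(2.69 + 4.68) = 2.72 h | 100% | about 70% |
| 8% by 12.75 h | √(2.69 + 5.98) = 2.94 h | 100% | about 54% |
| 10.2 h delays, 20% v 10% | √(2.69 + 13.01) = 3.96 h | 96% | about 70% |

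This table is a larger-SD sensitivity, not a consequence of the plan's inputs.

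**The case against.** A reader might infer that the trial would miss the planned effect if training mainly removes long delays. The planning inputs do not support this: at 1.02 h and SD 1.64 h, ranks lose almost nothing. The SD comes from a US observational study and could prove larger in Uganda, but the protocol does not say so.

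A reader might also infer that both intervals are certain to reach the Wilcoxon branch. The 24-hour eligibility limit bounds only accident-to-admission. The referral interval appears to arise only for patients with a referral decision, and no number, mean or SD is given for it, so the planned 425 per arm cannot be assumed there.

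Nor is Study Limitations a flat contradiction. Its t test can be the normal branch of the primary rule, or the t tests planned without a pre-test for the TEFS/TOMS and GOS scores. Still, calling the t test robust to non-normality removes the reason for the pre-test.

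The abstract and the Outcomes section do promise mixed models that could estimate a mean difference, and Multimedia Appendix 3, not shown here, holds the analysis metrics. The mean may therefore be estimated somewhere. That leaves the rule stated for the primary outcomes unranked against the models. It does not repair the rule.

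Finally, ranks have a real advantage for a small pure shift of skewed data (see the cost below).

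**Conclusion.** The point stands as a mismatch between the tested quantity and the quantity used for sizing and judging the trial. The test is left to the data. For accident-to-admission, the Wilcoxon branch is the likely outcome if times are right-skewed or rounded; for referral-to-discharge this is less certain. The cost is interpretive: a Wilcoxon rejection need not mean a difference in mean times (about 66% v 4% with equal means at the planned SD, under an assumed lognormal shape and unequal spread). It is not a loss of power at the planned effect and SD. Even a pre-test that rejects only sometimes leaves the primary question open until the data are seen. The simulations in steps 2 to 4 ignore clustering, which is a separate matter that affects both tests.

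**What to change.** In Primary (Process) Outcomes:
- Delete the Shapiro-Wilk and Levene steps as selectors of the test.
- For each interval, name one primary analysis: the difference in means with its 95% CI, from the cluster-accounting mixed model or hospital-level analysis already promised, with a small-sample t reference.
- Apply the 60-minute rule to that estimate.
- Keep the rank comparison as a sensitivity analysis only, reported as the chance that an intervention patient is quicker, with no 60-minute reading.
- Align the abstract, Outcomes and Study Limitations with this choice.

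A plain patient-level t test would not be enough. In simulation with 3 clusters per arm, either patient-level test had a type I error of about 19% at ICC 0.02.

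The cost is wording. Under the protocol's own inputs, no larger sample is needed (power 0.98 at ICC 0.02, 0.87 at ICC 0.05). The downside is lower power than ranks for a small pure shift of skewed data: at 0.3 h, about 75% v 99% before clustering. That shift is well below the 60-minute threshold. Because last follow-up has passed, the change should be dated and fixed before outcomes are examined by arm for the final analysis.
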